**Fig. 3 Fig3:**
[figure not shown]
Flowchart showing timing of randomization with respect to peer review and treatment planning. Contours must be finalized before randomization and may not be changed after randomization

**Planning Target Volumes (PTV):**

A 3–5 mm expansion is used around the combined CTVs (Table 1) to create the PTV, as per institutional setup and protocol.

##### Quality assurance (QA)

In order to ensure patient safety and effective treatment delivery, a robust QA protocol is incorporated. The following requirements must be completed for each patient:
Prior to randomization, each set of contours will be peer-reviewed, either by another individual radiation oncologist or at a team head and neck QA rounds.All dose delivery for intensity-modulated plans (including arc-based treatments) will be confirmed before treatment by physics staff.

Cone-beam CT and/or orthogonal x-rays will be used on a daily basis to verify treatment positioning, as per institutional standard practice.

##### Credentialling

Prior to enrolling patients, each centre will be given a sample CT dataset through secure file transfer protocol (FTP) for contouring, planning and physics QA. Enrollment can begin once the plan and QA have been approved at the London Regional Cancer Program. Centres who have been accredited for ORATOR [38] or ORATOR2 [40] are exempt from this requirement.

#### Participant discontinuation / withdrawal

Participants may voluntarily discontinue participation in the study at any time. If a participant is removed from the study, the clinical and laboratory evaluations that would have been performed at the end of the study should be obtained. If a participant is removed because of an adverse event, they should remain under medical observation as long as deemed appropriate by the treating physician.

#### Follow-up evaluation

Day 1 of follow-up will be the first day of radiotherapy. Follow-up will consist of history and physical examination with laryngopharyngoscopy, CT imaging of the neck ± thorax, QoL assessments and MBS. The follow-up schedule is shown in Additional file 2. Additional imaging or laboratory investigations should be carried out at the discretion of the oncologist, based on findings in the history or physical examination. Additional treatment (e.g. salvage treatment with surgery or further radiotherapy) is at the discretion of the treating physicians but will be recorded in the case report form.

#### Measurement of outcomes

**pN0 neck failure:** measured as time from randomization until disease recurrence in the initially pN0 hemi-neck(s). Patients with prior or simultaneous recurrence at the primary site or in the initially pN+ hemi-neck will be censored for this outcome as of that timepoint. The primary endpoint is a comparison of pN0 neck failure in Arm 2 vs. historical controls; this endpoint will also be compared between the two arms as a secondary endpoint.**OS:** measured as time from randomization until death from any cause.**DFS:** measured as time from randomization to either recurrence at any location or death, whichever occurs first. New primary tumours will not count as DFS events.**Local recurrence:** measured as time from randomization until disease recurrence at the primary site.**Regional recurrence:** measured as time from randomization until disease recurrence anywhere in the neck.**Locoregional recurrence:** measured as time from randomization until disease recurrence anywhere in the neck or at the primary site, whichever occurs first.**Recurrence in the pN0 neck without other locoregional recurrence:** measured as time from randomization until disease recurrence in the pN0 neck alone without recurrence at the primary site or pN+ neck.**Rate of salvage surgery and/or radiation in pN0 neck:** measured as time from randomization to salvage intervention (surgery ± radiation) in the pN0 neck. Freedom from unsalvageable neck recurrence will be reported as the time from randomization to development of a neck recurrence in the pN0 neck that could not be salvaged.**Feeding Tube Insertion:** Rate of feeding tube insertion after start of radiation (either gastric, gastrojejeunal, or nasogastric) and rate of feeding tube use at 1-year post-randomization. Patients with feeding tubes inserted prior to randomization will be censored for this endpoint.**Rate of failure in the clinically node negative neck**: for patients who have unilateral neck dissections, the cN0 neck may be treated with radiation or observed, at the discretion of the treating oncologist (see section 6). This is measured as the time from randomization to failure in the cN0 neck, and will be reported for the whole group of patients who had unilateral dissections, and also stratified by whether radiation was delivered to that area.

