#### Secondary endpoints

OSDisease-free survival (DFS)Local recurrenceRegional recurrenceLocoregional recurrenceRate of salvage treatment (surgery ± radiotherapy) in the pN0 neck, and freedom from unsalvageable neck recurrenceQoL at 1 year, assessed with the MD Anderson Dysphagia Inventory (MDADI) [28], the European Organisation for Research and Treatment of Cancer (EORTC) Quality of Life Cancer Patients general (QLQ-C30) [29] and head & neck (H&N35) scales [30], the EuroQOL 5-Dimension 5-Level (EQ-5D-5L) [31], and the Neck Dissection Impairment Index (NDII) [32]QoL measured at treatment completion and 6, 12, 15,18, 24, 30, 36, 42, 48, 54 and 60 months, measured with MDADI, EORTC QLQ-C30, H&N35, EQ-5D-5L and NDIIRate of feeding tube insertion after start of radiation (either gastric, gastrojejeunal, or nasogastric) and rate of feeding tube use at 1-year post-randomization.Swallowing function at 1-year, assessed by Modified Barium Swallow (MBS) study and measured by the Modified Barium Swallow Impairment Profile (MBSImP™©) score [33], the Dynamic Imaging Grade of Swallowing Toxicity (DIGEST™) score [34], and the Functional Oral Intake Scale (FOIS) [35].Toxicity, assessed using the National Cancer Institute Common Toxicity Criteria (NCI-CTC) version 4.03Rate of failure in the clinically node negative neck, if applicable (i.e. the undissected node-negative neck, for well-lateralized tumours).

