#### Statistical considerations

##### Sample size

The primary endpoint is the rate of relapse in the pN0 neck (i.e. the regional relapse rate in the pN0 neck) in Arm 2, compared to historical controls. All other endpoints are a comparison between Arm 1 and Arm 2.

It is generally accepted that a risk of nodal recurrence of 15–20% is sufficient to warrant radiation to a nodal basin, and therefore we wish to exclude a risk of regional recurrence in the pN0 neck of 20% at 2-years. Using a one-sided, one-sample binomial test, allowing for 5% dropout, a sample size in Arm 2 of 60 patients provides 83.1% power at a 0.05 significance level to detect a regional control rate in the pN0 neck of 92%, compared to an unacceptable level of 80%.

This sample size (30 in Arm 1 and 60 in Arm 2) also allows for > 80% power to detect a 10-point difference in the total MDADI score at 1 year (a secondary endpoint), assuming the scores are normally distributed with a standard deviation of 15 in each arm. It is generally believed that a 10-point difference in standardized QoL scores represents a clinically significant difference in QoL [42]. It is assumed that the QoL scores will be normally distributed with a standard deviation of 15 in each arm. The MDADI will be calculated as the composite score, but will also be reported for each of the subscales.

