#### Analysis plan

Patients will be analyzed in the groups to which they are assigned (intention-to-treat). Oncologic outcomes and OS will be calculated from date of randomization using the Kaplan-Meier method. A one-sided, one-sample binomial test will be used for the primary endpoint as described above. For actuarial comparisons between arms, the stratified log-rank test will be used (stratified by stratification factors). An two-sample T-test will be used to compare QoL scores at 1-year. The percentage of patients in each arm who experience a clinically significant QoL decline on the MDADI (10 points) will also be reported.

MBSImP™© scores will be compared at 1-year, including the total score, and the scores on the oral and pharyngeal subscales, using a two-sample T-test or a Wilcoxon rank sum test as appropriate. DIGEST™ and FOIS scores will be compared using the Chi-square test.

Pre-planned subgroup analysis will occur based on the stratification variables (nodal status [pN0 vs. pN+] and use of concurrent chemotherapy), as well as based on the neck dissection performed (unilateral vs. bilateral), and T-stage (T1–2 vs. T3–4). There will also be a pre-planned analysis based on the extent of nodes harvested in the pN0 neck (< 18 vs. 18 or more), depth of invasion of the primary tumour (< 4 mm vs. 4 mm or more), and photon versus proton treatment.

Multivariable Cox proportional hazards or logistic regression analysis, as appropriate, will be used to determine baseline and pathologic factors predictive of pN0 neck failure, DFS, OS, locoregional recurrence and salvage therapy. For the secondary endpoints involving QoL scales, linear mixed effects models will be used; for the MDADI, the total scores will be compared between the two arms, whereas for the EORTC QLQ-C30 and H&N35 scales, each of the subscales (e.g. pain, swallowing, etc.) will be compared between the two arms.

Rates of grade ≥ 2 toxicity and use of feeding tubes will be compared between arms using the Chi-square or Fisher’s exact test, as appropriate.

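### The rule that removes patients with a feeding tube before randomization fits new tube insertion but, as written, also covers tube use at 1 year, where their outcome can be observed

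*Protocol article*

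**What the plan says.** In the protocol article, Measurement of outcomes, the entry headed Feeding Tube Insertion contains two quantities. One is the rate of insertion after the start of radiation. The other is the "rate of feeding tube use at 1-year post-randomization". One sentence then closes the entry: "Patients with feeding tubes inserted prior to randomization will be censored for this endpoint". The Secondary endpoints list also carries both quantities as a single item.

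The Analysis plan section states that "use of feeding tubes will be compared between arms using the Chi-square or Fisher’s exact test", as appropriate. No time-to-event method is named for this endpoint. The same section begins with the general rule that "Patients will be analyzed in the groups to which they are assigned (intention-to-treat"). The article describes no separate 1-year rate that includes patients who already had a tube at randomization.

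**The concern.** The two parts are different kinds of outcome. Insertion is an incidence: a patient who already has a tube cannot have a first one placed, so leaving that patient out is sensible. Use at 1 year is a point prevalence: a patient with a baseline tube who is followed to 1 year is either using a tube or not. The rule discards that observation.

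Two things are lost. First, the reported 1-year rate applies to a narrower group than its name suggests, and it is too low for the randomized population if baseline-tube patients more often use a tube at 1 year. Second, the trial learns nothing from this endpoint about whether omitting radiation to the pN0 neck affects coming off a tube, because the only patients who could show it are removed.

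The situation is plausible here. Radiation must start within 7 weeks of surgery and randomization comes before treatment planning, so every patient is randomized within weeks of an oral cavity resection. The article does not say how many will have a tube at that time.

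**Working it through.** The article states no rate, sample size or power for this endpoint, so there is no figure of its own to reproduce.

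**Step 1: what censoring means here.** The planned test compares proportions. A patient censored at or before time zero contributes no follow-up, and a Chi-square or Fisher test has no place for censored data. The patient therefore leaves both numerator and denominator, which is exclusion.

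**Step 2: effect on the reported rate.** Let e be the share of patients with a tube at randomization, b1 their rate of tube use at 1 year, and b0 the rate in the others. Then:

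- rate in all patients = e × b1 + (1 − e) × b0
- rate reported under the rule = b0
- share of 1-year users left out = e × b1 / [e × b1 + (1 − e) × b0]

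The values of e, b1 and b0 are assumptions. The arm sizes of 30 and 60 come from the Sample size section, and everyone is taken as evaluable at 1 year.

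| e | b1, b0 | Reported | All patients | Users left out | Patients kept (Arm 1 / Arm 2) |
|---|---|---|---|---|---|
| 10% | 30%, 5% | 5% | 7.5% | 40% | 27 / 54 |
| 30% | 30%, 5% | 5% | 12.5% | 72% | 21 / 42 |
| 50% | 30%, 5% | 5% | 17.5% | 86% | 15 / 30 |
| 10% | 50%, 10% | 10% | 14% | 36% | 27 / 54 |
| 30% | 50%, 10% | 10% | 22% | 68% | 21 / 42 |
| 50% | 50%, 10% | 10% | 30% | 83% | 15 / 30 |

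Example, second row: 0.30 × 0.30 + 0.70 × 0.05 = 0.09 + 0.035 = 0.125, and 0.09 / 0.125 = 72%. If b1 = b0, the reported rate does not change.

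**Step 3: what is lost about coming off a tube.** Suppose e = 30%, b0 = 5% in both arms, and b1 = 40% in Arm 1 but 20% in Arm 2. The difference among all patients is 0.30 × (0.40 − 0.20) = 6 percentage points. The rule reports a difference of zero, because the whole effect lies in the excluded group.

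**Step 4: precision.** If event rates were the same with and without the excluded patients, the standard error of the difference would rise by a factor of 1/√(1 − e): 1.12 at e = 20% and 1.41 at e = 50%. That cannot be combined with Step 2, where the rates differ. With b1 = 30%, b0 = 5% and a common rate in both arms:

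- e = 20%: the rate in all patients is 10%. SE = √[0.10 × 0.90 × (1/30 + 1/60)] = 0.067 for all patients, against √[0.05 × 0.95 × (1/24 + 1/48)] = 0.054 for the restricted group, about 19% lower.
- e = 50%: the rate in all patients is 17.5%. SE = √[0.175 × 0.825 × (1/30 + 1/60)] = 0.085, against √[0.05 × 0.95 × (1/15 + 1/30)] = 0.069, again about 19% lower.

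Fewer patients contribute, but the direction of the change in standard error depends on the unknown rates.

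**The case against.** The entry is headed Feeding Tube Insertion and the rule speaks of tubes inserted before randomization, so the authors may have meant it for insertion only. That is plausible. As written, however, the sentence follows both quantities and refers to the endpoint as a whole, so the text needs correcting on either reading.

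Restricting 1-year use to patients who were tube-free at randomization can also be defended, as it separates tube need arising after randomization from need left over from surgery. That has merit as a supporting result. It does not justify making it the only 1-year rate under an unqualified name.

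Three stronger readings are tempting, and the document does not support them:

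- **Bias or a breach of intention-to-treat.** The exclusion rests on a characteristic fixed before randomization and applies identically in both arms. It moves nobody between groups and does not in itself bias the comparison. What changes is the population described.
- **A known loss of precision.** Step 4 shows that a fixed inflation of the standard error requires equal event rates, which contradicts the premise that the rate is understated.
- **Damage to a main functional outcome, in the patients for whom tube dependence matters most.** The article says neither. This is one of many secondary endpoints and has no power statement. The 1-year swallowing and oral intake measures (MBSImP, DIGEST, FOIS) carry no such stated exclusion, so baseline-tube patients still contribute functional information there.

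**Conclusion.** The point holds in a limited form and is minor. Applied literally, the rule drops patients with a pre-randomization tube from the 1-year use rate although their outcome can be observed. The rate then describes only patients tube-free at randomization, and it cannot show any effect on coming off a tube. It understates use among all randomized patients only if baseline-tube patients have higher 1-year use, which is likely but not documented. The size is unknown, because the article gives neither the share with a baseline tube nor any 1-year rate. Under the assumed values in the table, the gap runs from 2.5 percentage points (5% against 7.5%) to 20 points (10% against 30%), and it is zero if the two groups have equal rates. The primary analysis is untouched.

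**What to change.** Limit the rule to the insertion part and say that these patients are *excluded*, not *censored*. Report 1-year tube use by assigned arm for all randomized patients, overall and by tube status at randomization, with the planned Chi-square or Fisher's exact test. Show deaths before 1 year alongside in each arm, so that a low rate of tube use cannot be mistaken for good function when it reflects deaths. Restricting the main result to survivors would instead condition on an event after randomization. The rate in patients tube-free at randomization can stay as a supporting result.

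A logistic model adjusted for baseline tube status and both stratification factors is not needed and would be fragile. At the illustrative overall rates of 7.5% to 17.5%, 90 patients yield about 7 to 16 events (90 × 0.075 = 6.75; 90 × 0.175 = 15.75).

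The cost is a reworded sentence and one extra tabulation. Tube status at randomization must already be known to apply the present rule. The headline 1-year rate may look less favourable.

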#### Enrollment, randomization and allocation

Patients will be enrolled by dedicated clinical trials staff and/or the investigator at each participating institution. Patients will randomized in a 1:2 ratio to standard radiation volumes (Arm 1) vs omission to the pN0 neck (Arm 2). A permuted block design with two stratification factors will used with the size of the blocks known only to the statistician, stratified based upon overall neck nodal status (pN0 vs. pN+) and use of concurrent chemotherapy (yes vs. no). Randomization sequences are generated for each strata separately with a random number generator based on permuted block design. This gets formatted as a CVS file which gets uploaded into REDCap [41].

#### Statistical considerations

##### Sample size

The primary endpoint is the rate of relapse in the pN0 neck (i.e. the regional relapse rate in the pN0 neck) in Arm 2, compared to historical controls. All other endpoints are a comparison between Arm 1 and Arm 2.

It is generally accepted that a risk of nodal recurrence of 15–20% is sufficient to warrant radiation to a nodal basin, and therefore we wish to exclude a risk of regional recurrence in the pN0 neck of 20% at 2-years. Using a one-sided, one-sample binomial test, allowing for 5% dropout, a sample size in Arm 2 of 60 patients provides 83.1% power at a 0.05 significance level to detect a regional control rate in the pN0 neck of 92%, compared to an unacceptable level of 80%.

This sample size (30 in Arm 1 and 60 in Arm 2) also allows for > 80% power to detect a 10-point difference in the total MDADI score at 1 year (a secondary endpoint), assuming the scores are normally distributed with a standard deviation of 15 in each arm. It is generally believed that a 10-point difference in standardized QoL scores represents a clinically significant difference in QoL [42]. It is assumed that the QoL scores will be normally distributed with a standard deviation of 15 in each arm. The MDADI will be calculated as the composite score, but will also be reported for each of the subscales.

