## Methods / design

### Objectives

The objectives of this trial are to:
Compare regional recurrence rate to historical controls with omission of PORT to the pN0 neck.Compare oncologic outcomes, toxicity and QoL for PORT (± chemotherapy) based on standard treatment volumes (including the primary site tumour bed, dissected neck ± elective nodal regions) vs. PORT [± chemotherapy] that avoids treating the dissected, pN0 neck.

It is generally accepted that a risk of nodal recurrence of 15–20% is sufficient to warrant radiation to a nodal basin. Our hypothesis is that for patients with SCC of the oral cavity, T1–4 N0–3 (as per AJCC 8th edition) with at least one surgically dissected pN0 hemi-neck, the regional failure rate will be 20% or less at 2 years when treated with PORT omitting the pN0 neck.

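### The primary endpoint is defined as a censored time to event but tested with a one-sample binomial, which needs a known 2-year status, and only 5% dropout is allowed for

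*Protocol article*

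**What the plan says.** **Endpoint.** Measurement of outcomes defines pN0 neck failure as a time-to-event outcome ("measured as time from randomization until disease recurrence in the initially pN0 hemi-neck(s"). A patient whose disease recurs at the primary site or in the initially node-positive hemi-neck, before or together with the pN0 neck, is censored at that time.

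**Estimation.** The Analysis plan says: "Oncologic outcomes and OS will be calculated from date of randomization using the Kaplan-Meier method".

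**Test.** The same section says: "A one-sided, one-sample binomial test will be used for the primary endpoint as described above". The Sample size section gives the design: "Using a one-sided, one-sample binomial test, allowing for 5% dropout, a sample size in Arm 2 of 60 patients provides 83.1% power". The level is one-sided 0.05, with 92% regional control set against an unacceptable 80%. Its aim is "we wish to exclude a risk of regional recurrence in the pN0 neck of 20% at 2-years".

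**Hypothesis.** The Objectives word the target differently: "the regional failure rate will be 20% or less at 2 years". The abstract does likewise.

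**The concern.** The definition and the test do not fit together. A one-sample binomial test has no place for a patient whose follow-up for the endpoint ends before 2 years without a pN0 neck event. Such patients must be dropped, counted as controlled or counted as failures, and the article does not say which. Each choice tests a different quantity with a different power or error rate.

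The only allowance is 5% for dropout. Censoring for other locoregional recurrence comes on top of that, and so does death. The Background itself cites a pT1-T2 pN0 oral tongue series with 5% simultaneous locoregional recurrence in addition to 15% isolated regional recurrence. Those patients had no postoperative radiotherapy, so the figure is only indicative, but that single category would equal the whole allowance. Counting a simultaneous recurrence as controlled would also record a neck that has in fact recurred as a success.

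At stake is the main conclusion of a trial that omits treatment. The result could depend on a counting choice made late, and the Kaplan-Meier estimate and the binomial p-value could point in different directions.

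**Working it through.** **Inputs from the Sample size section.** Arm 2 has 60 patients with 5% dropout. The one-sided level is 0.05. The failure probability at 2 years is 0.20 (unacceptable) or 0.08 (to be detected).

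**Assumed, not in the article.** The 2-year incidence of a competing event (death, or other locoregional recurrence first) is taken as 10, 20 or 30%.

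**1. The plan's own figure.** Evaluable n = 60 × 0.95 = 57. The cut-off c is the largest number of failures with P(X ≤ c | n, 0.20) ≤ 0.05.
- P(X ≤ 6 | 57, 0.20) = 0.0451 and P(X ≤ 7 | 57, 0.20) = 0.0934, so c = 6.
- Power = P(X ≤ 6 | 57, 0.08) = 0.8313, which matches 83.1%.

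**2. The same calculation at other evaluable numbers.**

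| Evaluable n | Failures allowed | Exact error | Power |
|---|---|---|---|
| 60 | 6 | 0.031 | 79.8% |
| 59 | 6 | 0.035 | 80.9% |
| 58 | 6 | 0.040 | 82.1% |
| 57 | 6 | 0.045 | 83.1% |
| 56 | 5 | 0.021 | 71.0% |
| 54 | 5 | 0.028 | 73.8% |
| 50 | 5 | 0.048 | 79.2% |
| 48 | 4 | 0.025 | 66.2% |

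At n = 56, P(X ≤ 6 | 0.20) = 0.0510 just exceeds 0.05, so one allowed failure is lost. If the evaluable number K varies as Binomial(60, 0.95), average power is Σ P(K = k) × power(k) = 78.6%.

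**3. Censored patients dropped.** Let G be the crude 2-year incidence of a competing event, with 5% independent loss. Then K follows Binomial(60, 0.95(1 − G)), and the failure probability among those retained is 0.08/(1 − G).

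| G | Mean K | Failure probability among retained | Power, closed form | Power, simulated |
|---|---|---|---|---|
| 10% | 51.3 | 8.9% | 66% | about 65% |
| 20% | 45.6 | 10.0% | 48% | about 46% |
| 30% | 39.9 | 11.4% | 31% | about 30% |

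The simulation lets events and losses occur over time with constant hazards. Power falls for two reasons: fewer patients remain, and the failure proportion among them rises.

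If 8% is the net rate instead, use constant hazards λ = −ln(0.92)/2 and μ = −ln(1 − c)/2, with c the net competing risk. The crude failure probability is λ/(λ + μ) × (1 − exp(−2(λ + μ))), which is 7.6/7.2/6.7% for c = 10/20/30%. Power is 70/59/47% in closed form and about 67/56/46% in simulation.

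**4. Censored patients coded as controlled.**
- *Crude target.* At a crude incidence of 20% the failure probability is 0.20 by definition, so the test holds its level (3.4% averaged over K ~ Binomial(60, 0.95)).
- *Net target.* Put λ = −ln(0.80)/2 into the same formula. A net 20% becomes a crude 19.0/18.0/16.9%. Averaged over K ~ Binomial(60, 0.95), the error is 5.0/7.2/10.4%, that is about 5/7/10%.

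**5. The success bar.** The formal test passes at no more than 6/57 = 10.5% observed failures. The 20% in the hypothesis is the value to be excluded, not the observed rate that passes.

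**The case against.** The strongest reply is that the power figure is right and the gap is small. The 83.1% is exact at 57 evaluable patients, and basing power on the expected evaluable number is common practice. With 58 to 60 evaluable, power is still 80 to 82%. The fall at 56 is ordinary discreteness, and power is back at 79.2% with 50, so this is not a steady decline. All of this stands. A reader might infer that the stated power is wrong; it is not.

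A second reply is that coding competing events as non-failures gives a valid test of crude incidence, at a cost of only 2 to 3 power points against a cumulative-incidence rule. This also stands. A reader might set an error of 9 to 13% for the binomial (net 20%, exactly 57 evaluable, competing risk 20 or 30%) against 3.4 to 3.8% for a cumulative-incidence limit. That contrast mixes targets: the first figures are at a net rate of 20%, the second at a crude rate of 20%. At a net 20% with 20/30% competing risk, simulation gives 8.4/11.3% for the cumulative-incidence rule and 7.4/10.0% for the success-coded binomial.

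A third reply is that nothing says censored patients will be dropped, and that the Analysis plan specifies intention-to-treat. True: dropping is one reading, not the stated plan.

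A fourth is that counting rules belong in the SAP, which is not shown. This is only partly persuasive. The article itself fixes both a censoring rule and a test that cannot use it, so a counting rule added later would in effect choose the estimand.

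Finally, a reader might take the hypothesis wording to make 11/57 observed failures a success, with a 53% false-success rate at a true 20%. No section sets that rule. The Sample size section is clear that 20% is to be excluded.

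**Conclusion.** The mismatch is real and should be resolved before analysis. The primary endpoint is a censored time to event, while its test needs a known 2-year status for every patient. The stated power is correct for its scenario but sits at a local peak; under the plan's own 5% dropout, taken as random, it averages 78.6%.

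The size of the harm depends on the unstated handling. Dropping censored patients leaves power of roughly 65/46/30% at 10/20/30% crude competing incidence, or about 67/56/46% on the net scale. Coding them as controlled is sound for crude incidence, but anti-conservative for the net rate that Kaplan-Meier with such censoring estimates (about 5/7/10%). It would be too strong to say that most of the power is always lost: at 10% competing incidence about two thirds remains, and under the success coding power is not lost in this way.

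These figures assume constant hazards, 5% loss independent of outcome, and a competing incidence that the article does not give. The mismatch itself rests on the text alone.

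**What to change.** Choose one estimand and test it in all Arm 2 patients.

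- **If crude incidence is the target:** use the 2-year cumulative incidence of pN0-neck recurrence (Aalen-Johansen). Treat death and prior primary-site or node-positive-neck recurrence as competing events, and censor loss to follow-up. State explicitly how a simultaneous recurrence counts, and reconcile that with the censoring rule in Measurement of outcomes. Declare success if the one-sided 95% upper limit is below 20%, and keep the binomial as a sensitivity analysis. Restate power as about 80-82% (simulated with 60 patients, 5% loss, 0-30% competing incidence and a crude rate of 8%).
- **If the net rate is the target:** use the upper limit of the 2-year Kaplan-Meier failure estimate, and compute power for that rule.

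In either case, align the hypothesis wording in the abstract and Objectives with the aim of excluding 20%. This is a wording change only.

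**Cost.** A protocol or SAP text change, a slightly lower stated power and minor extra analysis work. No additional patients or data are needed.
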